### 7 day accelerometer

This will be attached to the participant at the end of the study visit. It consists of a wrist worn accelerometer similar in design to a wrist worn watch. Wrist worn accelerometers have high compliance and reliability and are validated measures of physical activity. Participants will be asked to wear the accelerometer for 7 days.

Stamped addressed envelopes will be provided to return devices.

### Visit 4. Exit Interview

We will conduct structured interviews with participants in both arms who consent to participate in the optional exit interview to assess their experience of study participation and to identify and explore factors related to the successful (or unsuccessful) implementation of the intervention. This will provide data regarding the views of participants as to the acceptability of supervised exercise and self-monitored physical activity behavior change.

Participants in both arms will be interviewed to explore barriers and facilitators to supervised exercise, self-monitoring physical activity and trial participation. The control group will be interviewed to allow comparison of patient experience in the two arms.

The structured interviews will take approximately 10-15 minutes. There will be 5 questions for both groups, and an additional 5 questions in the intervention group.

An important focus of the interviews will be on identifying: perceived barriers; where similarities and differences in perception lie; appropriate behaviors and information sharing between participant and intervention team; and participant satisfaction. We will use a structured interview approach with free text options, as this provides a reproducible format for consistency across interviews, while also allowing for further (free text) explanation. Structured responses will be entered on to a pre-coded scoring sheet. Free text responses will be audio-recorded and transcribed in order to capture all participant experiences.

All participants being enrolled into the trial will be asked if they consent to participate in this optional exit interview. The interview will be conducted by a researcher independent to the intervention delivery team. Participants will be given the option of a face to face interview at the end of study visit 4 or a telephone interview at the participants’ convenience.

## Sub-Study Visits: Circulating biomarker validation and evaluation visit 1 and visit 2

### Recruitment of participants for TEPHRA blood validation sub-study

A sub-cohort of healthy individuals will be invited via poster advertisement with primary advertising locations including: Oxford University Hospitals NHS Foundation Trust, University of Oxford Colleges and the Oxford Brookes University, to participate in a sub-study for blood cell and circulating biomarker evaluation.

The additional cohort of participants (n=20) will be invited to the blood cell and circulating biomarker validation and evaluation study. Participants will be asked to attend the Oxford Cardiovascular Clinical Research Facility at the John Radcliffe Hospital in Oxford having consumed only water for 4 hours beforehand.

### Visit 1

### Consent (10 mins)

Participants will be asked for their consent to take part in the sub-study. Personal data as follows will be collected and stored separately. This is to facilitate contact with participants during the study, and to arrange baseline and follow-up visits:

- Forename and surname
- Address including postcode
- Date of Birth
- Telephone number
- Email address

Participant examination will be completed post-informed consent. If an exclusionary item is verified during the visit, the investigator will notify the participant. No additional research procedures will be performed, and, with the participant’s consent, the participant will be referred for clinical follow-up.

### Eligibility screening (5 mins)

Participants will have their blood pressure checked after 5 minutes rest using the automated mode of a sphygmomanometer. Three blood pressure readings will be taken at intervals of 1 minute. Clinic blood pressure above 159/99 mmHg will be excluded and no additional procedure will be performed.

### Study procedures

### Physical examination (10-15 mins)

Anthropometric measurements including height, weight and bio-impedance measurements will be collected. Participants will have their blood pressure taken again for the second visit. Participants will have their blood pressure checked after 5 minutes rest using the automated mode of a sphygmomanometer. Three blood pressure readings will be taken at intervals of 1 minute.

### Blood sampling (10 mins)

If a participant is eligible, a venous fasting blood sample (approximately 30mls) will be taken at rest for a) whole blood, plasma and serum lipid and inflammatory marker analysis, b) analysis of biochemistry and metabolism c) analysis of biomarkers associated with inflammation, angiogenesis and endothelial activation.

Blood samples will be centrifuged, and plasma, serum, cells and DNA stored. Samples collected will be used for several experiments including looking at genes and protein expression to ensure the reproducibility and validity between the samples collected from the same individual from two independent visits. All samples will be retained in a secure environment for future analysis which will be performed in batches. Samples will be stored in an anonymous format in the Cardiovascular Clinical Research Facility, Division of Cardiovascular Medicine, University of Oxford at the John Radcliffe Hospital site and Wellcome Centre for Human Genetics under the custodianship of [name]. Relevant Human Tissues samples will be destroyed at the end of study unless consent has been obtained from the participant to retain their samples for future research. In this case, samples will be transferred to another ethically approved study and a copy of the consent will be kept. Non-relevant Human Tissues samples will be kept indefinitely.

### Visit 2

Participants will be invited back exactly one week later for the follow-up visit (visit 2). Study procedures will be as per listed under visit 1.

## Additional sample collection and handling

The sample collection and handling are described elsewhere in the protocol. Upon the completion of the studies, samples from the YACHT 2 Study (14/SC/0275) and Expresso (14/SC/0281) will be transferred to this study should there be consent from the participant to use samples in future ethically approved studies in order to assess blood biomarkers. Copies of the consent forms will be retained with the samples.

## Discontinuation/Withdrawal of Participants from Trial

Each participant has the right to withdraw from the trial at any time. In addition, the Investigator may discontinue a participant from the study at any time if the Investigator considers it necessary for any reason including:

- Pregnancy
- Ineligibility (either arising during the study or retrospectively having been overlooked at screening)
- Significant deviation from the study protocol
- Withdrawal of Consent
- Loss to follow up
- Contraindication to exercise participation

If participants withdraw from the study the study investigators will ask the participants if they can make use of the information that has been collected up to the time of withdrawal to facilitate intention to treat analysis. Participants may withdraw consent for any use of their samples or data at any time. If this is the case we will destroy any identifiable samples or information we hold about the participant. Participants do not need to provide any reason for withdrawal; should they freely offer a reason it will be recorded in the CRF/eCRF. The research team may recruit additional participants to replace participants who have withdrawn.

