## Procedures for Recording Adverse Events

All AEs occurring during the trial / or until completion of the final study visit that are observed by the Investigator or reported by the participant, will be recorded on the CRF, whether or not attributed to the exercise intervention.

The following information will be recorded: description, date of onset and end date, severity, assessment of relatedness to exercise intervention, other suspect drug or device and action taken. Follow-up information should be provided as necessary.

The severity of events will be assessed on the following scale: 1 = mild, 2 = moderate, 3 = severe.

AEs considered related to the trial treatment as judged by a medically qualified investigator or the Sponsor will be followed either until resolution, or the event is considered stable.

It will be left to the Investigator’s clinical judgment to decide whether or not an AE is of sufficient severity to require the participant’s removal from treatment. A participant may also voluntarily withdraw from treatment due to what he or she perceives as an intolerable AE. If either of these occurs, the participant must undergo an end of trial assessment and be given appropriate care under medical supervision until symptoms cease, or the condition becomes stable.

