# STATISTICS AND ANALYSIS

## Description of Statistical Methods

The analysis will be carried out on the basis of intention-to-treat (ITT). This is, after randomisation, participants will be analysed according to their allocated intervention group irrespective of what they actually receive.

Patient demographic characteristics and other baseline information will be summarised by treatment group. Numbers (with percentages) for binary and categorical variables and mean (standard deviation), or median (interquartile or full range) for continuous variables will be presented. Normality of variables will be assessed by visual assessment of the normality curves and the Shapiro-Wilk test. The analysis of the primary outcome will be assessed using analysis of covariance (ANCOVA) adjusting for baseline values and minimisation factors used in the randomisation process. Results will be presented as adjusted mean difference in change in ambulatory blood pressure between randomised groups at 4 months with 95% confidence intervals (CI) and associated two-sided p value. The analysis of secondary outcomes will also be done using analysis of covariance (ANCOVA) to establish a co-variant model to examine the effect of cardiac structure, vascular function and lifestyle behaviours on exercise capacity. Outcomes measured on more than one occasion will be analysed using a mixed effects model. The data collected from the sub-study will be analysed using paired and independent T-test. If the model assumptions are not met and evidence of departure from Normality is observed, transformations of the data will be employed or non-parametric tests will be carried out. Statistical analysis will be carried out using STATA or SPSS statistical software.

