## Exercise Associated Musculoskeletal Injury

Study participants entering the exercise training arm will be instructed on injury prevention practice including warm-up and stretching exercises. Participants will be encouraged to maintain regular preventive lower limb exercise demonstrated during the supervised sessions. The study team includes training sports and exercise medicine physicians experienced in injury prevention and rehabilitation. If there are any concerns regarding a participant’s safety to continue in the trial secondary to injury, they will be asked to stop training. Safety to continue in the trial will be reviewed by trained and qualified personnel identified in the delegation log and the outcome will be discussed with their primary care team as appropriate.

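### Sections 8.9 and 10.2 do not separate stopping the exercise programme from leaving the study, so 16-week blood pressures that the intention-to-treat analysis needs can be lost, mainly in the exercise arm

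*Supplement*

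**What the plan says.** - **Section 8.9** (Discontinuation/Withdrawal): "the Investigator may discontinue a participant from the study at any time if the Investigator considers it necessary for any reason including" a list that contains "Significant deviation from the study protocol" and "Contraindication to exercise participation", along with pregnancy, ineligibility, withdrawal of consent and loss to follow-up. The exit is from the study, not only from the exercise. What counts as significant is not defined. For people who withdraw, the section asks permission to use data gathered up to that point. It plans no measurement afterwards.
- **Section 8.9**, on replacement: "The research team may recruit additional participants to replace participants who have withdrawn". Section 11.2 repeats the option for drop-outs.
- **Section 10.2** (adverse events), on removal or voluntary withdrawal from treatment: "If either of these occurs, the participant must undergo an end of trial assessment".
- **Section 14.5** (musculoskeletal injury): a participant about whom there is concern stops training, and then "Safety to continue in the trial will be reviewed by trained and qualified personnel identified in the delegation log". Here stopping training and staying in the trial are two decisions.
- **Section 11.1**: "participants will be analysed according to their allocated intervention group irrespective of what they actually receive".
- **Supplement, Section 1**: the primary analysis was carried out on complete cases.

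**The concern.** An analysis by allocation needs the 16-week ABP of people who stopped exercising or departed from the programme. Sections 8.9 and 10.2 offer a route by which those same people leave the study before it is measured. A complete-case ANCOVA then drops them.

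The route is not neutral between arms. The trial is open. The exercise arm has three sessions a week for 16 weeks, with attendance monitored weekly by the study team (Section 9). Controls receive educational material. Deviation and exercise contraindication will therefore arise mainly in the exercise arm, and the decision to discontinue is made with the allocation known. If those removed would have had a different 16-week blood pressure from those retained, the analysed exercise group no longer represents everyone allocated to exercise.

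Replacement restores the number of participants but not the missing outcomes. Neither replacement sentence says that the person replaced stays in the intention-to-treat population.

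**Working it through.** **1. The plan's own figures.** Section 11.2 uses a 5 mmHg difference, SD 11.3 mmHg, 80% power and 5% significance (taken as two-sided). A two-sample t calculation gives 81.15 per arm, rounded up to 82, or 164 in total. Allowing for 18% attrition, 164 / (1 − 0.18) = 200. Both figures reproduce. The attrition allowance and the replacement option deal with how many outcomes are missing, not with whose.

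**2. The clauses side by side.**

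| Event | Consequence stated | Later 16-week ABP sought? |
|---|---|---|
| Significant deviation, exercise contraindication (8.9) | May be discontinued from the study | Not stated |
| Off treatment for an adverse event (10.2) | End-of-trial assessment | Not stated |
| Training stopped after injury (14.5) | Continuation in the trial reviewed separately | Possible |
| Analysis (11.1) | By allocation, whatever was received | Required |

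Sections 10.2 and 14.5 treat the same kind of event differently, and neither 8.9 nor 10.2 meets the need in 11.1.

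**3. Missing outcomes.** Counts are from eTable 4; the arm totals agree with the baseline counts in eTable 2. The last column is the number with the 16-week exercise test (peak oxygen uptake) minus the number with 16-week ABP. This is the smallest number who can have been tested but have no ABP.

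| Group | Baseline | 16-week ABP | Missing | 16-week test | Tested, no ABP (at least) |
|---|---|---|---|---|---|
| Exercise, ≥3 h/week | 45 | 43 | 2 (4%) | 45 | 2 |
| Exercise, <3 h/week | 57 | 33 | 24 (42%) | 39 | 6 |
| Exercise, all | 102 | 76 | 26 (25%) | 84 | 8 |
| Control | 101 | 84 | 17 (17%) | 92 | 8 |

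Fisher's exact test gives p<0.001 for low against high volume, and p=0.17 between arms. The per-protocol counts in eTable 3 point the same way. Of 82 compliers, 71 (87%) have 16-week ABP. By subtraction, 5 of the other 20 (25%) do. Compliers are 82/102 = 80% of those allocated to exercise and 71/76 = 93% of those with data.

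**4. How many losses could be removals.** A person who took the 16-week test had not been removed before it. In the low-volume group, at most 24 − 6 = 18 losses could be earlier removals. In the high-volume group the figure is 2 − 2 = 0, and in control at most 17 − 8 = 9.

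**5. Possible shift.** If m of the 102 exercise participants differ on average by d mmHg from what missing at random predicts, the arm mean shifts by (m/102) × d. The documents do not give d, so it is an assumption. With m at its upper limit of 18:

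- d = 2: 18/102 × 2 = 0.35 mmHg
- d = 5: 18/102 × 5 = 0.88 mmHg
- d = 6: 18/102 × 6 = 1.06 mmHg

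For scale, 2 mmHg is the reduction that the protocol's Background links to lower stroke risk, and 5 mmHg is the design effect. The gap between the exercise arm's 70th and 50th systolic quantiles in eTable 1 is 131 − 125 = 6 mmHg. If no loss was a removal, m = 0 and this mechanism contributes nothing.

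**The case against.** **Removal is discretionary.** Section 8.9 says the investigator may discontinue, and stopping exercise is not itself a listed ground. Section 14.5 shows that exit need not follow. This stands: the text permits the loss without requiring it. It does not answer the lack of any plan to measure ABP once someone has been discontinued. Section 8.6 schedules the 16- and 52-week visits, but does not say that they apply to a person no longer in the study.

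**A reader might infer that the comparison became one among adherers.** The documents do not support that. Of the 76 exercise participants with 16-week ABP, 33 were in the low-volume group and, by subtraction, 5 were outside the per-protocol set.

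**A reader might infer from eTable 4 that the rule produced the missing data.** It cannot show this. The volume groups are post hoc and based on exercise completed, so someone who left early can be low-volume because of leaving. At least 8 exercise losses and 8 control losses had the 16-week test. No count of discontinuations by reason is given. The supplement calls withdrawals few and mostly unrelated to the intervention, although it also reports more of them in that arm.

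**A reader might infer that replacement refills the exercise arm with adherent people.** Section 8.4 allocates eligible participants 1:1 by minimisation, and nothing directs replacements to one arm. The randomised totals, 102 and 101, show no refilling.

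**Not every ground is one-sided.** Ineligibility missed at screening can arise in either arm. A contraindication to exercise could also affect controls, who repeat the exercise test. Hence mainly, not only, the exercise arm.

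**Sensitivity analyses were done.** Multiple imputation on all 102 and 101 gives an adjusted systolic difference of 0.0 (−2.6 to 2.7), and quantile imputation moves the arms in opposite directions. These are useful. The multiple imputation, however, used only the analysis-model variables, so exercise volume did not inform it. Modelling is also a weaker remedy than collecting the outcome.

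**Conclusion.** The point holds as a fault in the protocol's wording. Sections 8.9 and 10.2 let a departure from the exercise programme become a departure from the study, Section 14.5 keeps the two apart, and Section 11.1 needs outcomes that the first two sections make no provision to collect. In an open trial with a demanding programme in one arm only, this can tilt a complete-case comparison towards adherers.

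The size is bounded but not known. Up to 18 of 102 exercise participants could have been lost in this way before the 16-week test. A 5 mmHg departure from missing at random among all 18 would shift the exercise mean by about 0.9 mmHg, roughly a sixth of the 5 mmHg design effect (0.88/5 = 0.18). This assumes that the counts in eTable 4 are participants with observed values, that all 18 were removals, and that control losses add no shift of their own. The direction is undetermined. The tables establish that missingness goes with low exercise volume. They do not establish that investigator removal is the reason.

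**What to change.** - Reconcile Sections 8.9, 10.2 and 14.5 so that stopping the exercise programme or deviating from the protocol does not by itself end study follow-up.
- Seek the scheduled 16- and 52-week ABP from every randomised participant unless consent is withdrawn or contact is lost. Clinical decisions about exercise and other study procedures stay as they are.
- State in Sections 8.9 and 11.2 that a replaced participant remains in the intention-to-treat population, and that a replacement is newly randomised through the procedure in Section 8.4.
- Report discontinuations by arm and reason, separating investigator decisions from participant withdrawals. For data already collected, this is the part that can still be done, and it would show how many of the possible 18 were removals.

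The cost is protocol wording plus some extra effort to bring people back to visits that are already scheduled.

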## Definition of End of Study

The end of study is the date of the last visit or telephone interview if completing an optional exit telephone exit interview of the last participant.

# INTERVENTIONS

# Supervised Aerobic Exercise and Self-Monitoring Physical Activity Intervention

# (See Appendix E)

**Supervised Exercise**

Participants in the intervention arm will complete 16 weeks training with weekly supervised aerobic interval sessions, 3 sessions per week, duration 40-60 minutes, plus 15 minutes warm-up and cool-down (total duration 70-90 minutes). Participants will be provided with a 4 month gym membership, training will be co-ordinated by the study team in collaboration with the team from the Movement Science Department at the Oxford Brookes University. Gym membership will be secured at facilities local to the participant and pre-approved by the study team. Attendance and progress during the supervised intervention will be monitored weekly by the study team.

Exercise prescription will be based on 60-80% maximal aerobic capacity defined using heart rate response during peak cardiopulmonary exercise testing at baseline. Heart rate monitors will be used to maintain intensities of sessions. The supervised intervention replicates similar strategies identified during systematic review of the randomised control literature delivering exercise intervention for blood pressure reduction^48,49^. The minimum dose to start effecting positive changes in cardiovascular fitness is estimated to be 40 minutes of moderate intensity sessions three times per week. Dose exposure will be titrated via increased intensity and duration of exercise as tolerated.

**Self-monitored physical activity and support for sustained behaviour change**

During the 16 week supervised exercise intervention training instructors and intervention staff will support global increase in self-monitored physical activity. Instructors will support the three most effective behaviour change strategies to promote increased physical activity, including participant self-monitoring, goal setting and regular feedback^50,51^. Participants will be provided with accelerometer-based activity monitors, equivalent to the Fitbit or similar device, to allow self-monitoring and target increased physical activity outside of supervised sessions.

The daily physical activity target will be based on the recommended guideline of daily step counts of 10,000 steps per day. Increasing steps counts will be facilitated by titrating a proportional increase from baseline activity to achieve the minimum target of 10,000 steps.

Participants will be consented to allow investigators access to the data collected from wear of the Fitbit or similar device. The information will be used to facilitate feedback on physical activity, goal setting and maintenance of physical activity behaviours.

Following the supervised intervention participants will be encouraged to continue to use their activity monitor and maintain physical activity goals. Remote support will be provided to facilitate feedback and maintenance of physical activity. The intervention team will review continued use of the activity monitor and activity targets at a minimum of 2 weeks. If physical activity is declining or wear time has declined participants with be contacted and offered support to re-engage with behavioural targets. Contact will be maintained via email, text messaging and phone calls. If required, participants will be offered face-to-face support, communication will incorporate motivational strategies to maintain activity goals.

